## Discussion

This is a study comparing the efficacy and safety of single frozen blastocyst transfer with single fresh blastocyst transfer in women with a good prognosis. We plan to enroll 1618 subjects from more than 20 academic IVF centers in China. The enrollment began in August 2016. At the time of manuscript preparation, more than 300 subjects have been enrolled. The result of this large multicenter randomized trial will provide level I evidence for the strategy of single frozen blastocyst transfer in patients with a good prognosis.

Elective embryo cryopreservation followed by frozen embryo transfer, i.e., the freeze-all strategy, has attracted increasing attention and has been considered as a potential innovation of IVF treatment [15]. However, there are still great gaps in the literature to illuminate the risk/benefit ratio of this strategy, which includes multiple steps of treatment [19]. Four randomized trials compared frozen versus fresh embryo transfer [18, 20–22]. However, the stage and the number of embryos transferred varied among studies. Embryos were frozen by the slow-freezing method at 2PN stage in the earlier studies [20–22]. In a recent study in women with PCOS, embryos were vitrified at the cleavage stage, and two embryos were transferred [18]. There are several striking differences in uterine condition and embryo characteristics between cleavage-stage embryo transfer and blastocyst transfer. It was observed that uterine contractility had been significantly decreased at the time of fresh blastocyst transfer compared with that at the time of fresh cleavage-stage embryo transfer, and high-frequency uterine contraction was suggested to negatively impact the outcome of IVF via the dislocation of the embryo or disruption to the interaction between embryo and endometrium [23, 24]. Additionally, there were concerns regarding epigenetic modifications during blastocyst culture. A meta-analysis pooling six observational studies demonstrated that singleton pregnancies following blastocyst transfer were associated with higher risks of preterm birth and congenital anomalies compared with those following cleavage-stage embryo transfer [25]. Whether these differences necessarily translate to less superiority of frozen blastocyst transfer over fresh blastocyst transfer is unknown.

In women with a good prognosis, i.e., those who are defined as young and undergoing their first IVF cycle and obtaining four or more day-3 transferrable embryos in this study, eSET is recommended to reduce the risk of multiple pregnancies. However, the adoption of this policy has been slow due to concerns about the diminished pregnancy rate. Extending embryo culture to the blastocyst stage to improve embryo selection has been demonstrated as an effective measurement. Whether replacing the well-selected embryo into a more physiological uterine environment could further increase the chance of live birth of eSET is of great clinical significance. This study is expected to provide a reliable answer.

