#### Randomization

Block randomization is used to assign subjects to treatment groups with a 1:1 ratio. The randomization is stratified by study site. The sequence of randomization has been generated by biostatisticians in data coordinator center with SAS software version 9.2 (SAS Institute, Cary, NC, USA). The original sequence is safely kept by the staff in the data coordinator center, and it has been input into the online central randomization system by these staff members, who are not involved in enrolling subjects. The online sequence is not accessible to any investigators or study coordinators. If a subject fulfills the enrollment criteria, the authorized investigator or study coordinator will login the password-protected account to get the assignment for her. After randomization, both subjects and investigators are informed about the assignments.

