### Data analysis

#### Sample size calculation

Based on the retrospective data from our IVF clinic, the live birth rate following single fresh blastocyst transfer in patients younger than 35 years is about 50%. It was assumed that an absolute difference of 10% in live birth rate will be of clinical significance. We aim to test a difference of 10% of live birth rate between treatment groups (i.e., 50% in the fresh group and 60% in the frozen group) at a significance level of 0.01 with a statistical power of 90%. The minimal sample size calculated is 735 for each group. In consideration of a dropout rate of 10%, we will enroll 817 subjects in each group.

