#### Data analysis plan

The primary analysis will use an intent-to-treat approach to examine differences in the singleton live birth rate in the two treatment arms using the Pearson chi-square test. Safety parameters and secondary efficacy parameters, such as pregnancy rate, OHSS rate, and other rates, will be analyzed using the Pearson chi-square test. A secondary per-protocol analysis will be performed according to the actual treatment that subjects received. Continuous data were expressed as mean ± standard deviation with a Wilcoxon rank sum test for testing between-group differences. Categorical data were represented as frequency and percentage; differences in these measures between treatment groups were assessed by chi-square analysis, with Fisher’s exact test for expected frequencies less than 5.

The flow chart of this study is given in Fig. 2, and the SPIRIT checklist is included as Additional file 1.

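### The Discussion's enrolment total of 1618 contradicts the 817 per group (1634) set in the sample size section; a minor but certain discrepancy

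*Protocol article*

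**What the plan says.** The Sample size calculation section sets the design assumptions: live birth rates of "50% in the fresh group and 60% in the frozen group", tested "at a significance level of 0.01 with a statistical power of 90" percent. It then reports the result, "The minimal sample size calculated is 735 for each group", and the allowance for losses: "In consideration of a dropout rate of 10%, we will enroll 817 subjects in each group". The Randomization section fixes equal allocation: "Block randomization is used to assign subjects to treatment groups with a 1:1 ratio". The total implied is 2 × 817 = 1634, although the article never prints that number.

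The Discussion gives a different total: "We plan to enroll 1618 subjects from more than 20 academic IVF centers in China". It adds that more than 300 women had been enrolled when the manuscript was prepared, and the Trial status section says that enrolment was still ongoing. The article does not mention the gap between the two totals.

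**The concern.** Both statements describe planned enrolment for the same two-arm trial. Neither is given as approximate, and neither rounds to the other. Planned enrolment is a figure that the trial relies on. With two published totals, a later reader cannot tell whether a trial that closed at 1618 was complete or 16 women short, or whether one that closed at 1634 was complete or over-enrolled.

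There is also a question of adequacy. The sample size section treats 735 per group as a minimum and enlarges it so that this minimum survives 10% dropout. A smaller total may not leave that many women, so it is worth checking which of the two totals meets the plan's own requirement.

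**Working it through.** **Inputs**

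- From Sample size calculation: p1 = 0.50, p2 = 0.60, significance level 0.01, power 0.90, minimum 735 per group, dropout 10%, enrolment 817 per group.
- From Randomization: 1:1 allocation.
- From Discussion: total enrolment 1618, which is 809 per group at 1:1.
- Assumption: the article does not say whether the test is one- or two-sided. Two-sided is used here because it reproduces the stated 735; a one-sided calculation gives 643.

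**Step 1. Reproduce the minimum.** With pooled variance under the null and no continuity correction,

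n = [z(0.995) × √(2 p̄(1 − p̄)) + z(0.90) × √(p1(1 − p1) + p2(1 − p2))]² / (p2 − p1)²,

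where p̄ = 0.55, z(0.995) = 2.576 and z(0.90) = 1.282.

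- First term: 2.576 × √0.495 = 1.812.
- Second term: 1.282 × √0.49 = 0.897.
- n = (2.709)² / 0.01 = 734.05 when unrounded values are carried, rounded up to **735**.

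This matches the article exactly.

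**Step 2. Reproduce the dropout allowance.** To keep 735 after losing 10%, divide by the fraction retained: 735 / (1 − 0.10) = 816.7, rounded up to **817** per group. The total is 2 × 817 = **1634**. This also matches the sample size section.

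**Step 3. Look for a route to 1618.** Multiplying up instead of dividing gives 735 × 1.10 = 808.5, rounded up to 809 per group, and 2 × 809 = **1618**. The match is exact.

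**Step 4. Compare the two totals at 10% dropout.** Power is from the same two-proportion formula.

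| Total enrolled | Per group | Left per group after 10% dropout | Power |
|---|---|---|---|
| 1634 | 817 | 1634 × 0.9 / 2 = 735.3 | 90.1% |
| 1618 | 809 | 1618 × 0.9 / 2 = 728.1 | 89.7% |

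Power at exactly 735 per group is 90.0%. The total of 1618 falls short by 735 − 728 = 7 per group, or 14 overall.

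**Step 5. Dropout that 1618 can absorb.** 1 − 1470/1618 = 9.1%, against the planned 10%.

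**Step 6. Relative size of the gap.** (1634 − 1618) / 1634 = 16/1634 = 1.0%.

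**The case against.** The strongest reply is that the design itself is sound. The section that sets the sample size is correct at both steps, and the stray total stands only in a narrative sentence of the Discussion. The gap is 1.0% of the total and costs about 0.3 percentage points of power. That is far less than the uncertainty in planning inputs such as a control rate of about 50% and a round 10% dropout. This stands, and it is why the point is minor.

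A second reply is that the shortfall depends on how losses are handled. The primary analysis is by intention to treat and compares "differences in the singleton live birth rate in the two treatment arms using the Pearson chi-square test". If all 809 women per group were analysed and the 50% and 60% rates held, the same formula gives about 93% power. This also stands. The figure of 728 applies only if the full 10% is lost from the analysis, though that is the premise of the article's own dropout allowance.

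Three stronger readings are tempting, and the article does not support them:

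- **That the dropout rate was wrongly multiplied on.** The match with 2 × 809 makes this plausible, but the article does not say how 1618 arose. A superseded or mistyped total is also possible.
- **That recruitment will stop at 1618.** The Randomization section gives no list length or cap, and nothing shows which total the sites use.
- **That the trial is underpowered.** A loss of 0.3 points in the worse case is not a material loss of power.

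None of these replies removes the contradiction between the two totals.

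**Conclusion.** The point holds as a minor internal contradiction in the enrolment target. The two figures cannot both be the plan, and only 1634 follows from the stated 735 per group and 10% dropout.

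The size of the consequence is conditional. It assumes a two-sided test at 0.01, the article's own event rates, 1:1 allocation and 10% of women missing from the analysis. On those terms 1618 leaves about 728 per group against a minimum of 735. No choice of test, error rate or interpretation of the result depends on the difference.

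**What to change.** Replace 1618 with 1634 in the Discussion, so that the article states one total and it agrees with the sample size section. This corrects one number while enrolment is still open. It adds 16 women to the total printed in the Discussion and none to the sample size section's own target.

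If the sponsor confirms that 1618 is the real operational target, leave the Discussion as it is. Restate the sample size section as 809 enrolled per group, about 728 evaluable per group after 10% dropout, and about 89.7% power. The cost is a slightly lower stated power. This route should be taken only on that confirmation, because it would otherwise rewrite a correct calculation to fit an unexplained total.

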## Trial status

The enrollment of this study is ongoing at the time of manuscript submission.

## Abbreviations

eSET: Elective single embryo transfer
GnRH: Gonadotropin-releasing hormone
hCG: Human chorionic gonadotropin
ICSI: Intracytoplasmic sperm injection
IVF: *In vitro* fertilization
OHSS: Ovarian hyperstimulation syndrome
PCOS: Polycystic ovary syndrome
rFSH: Recombinant follicle-stimulating hormone
